### Proposed analyses

Analyses will be performed according to the intention-to-treat principle and we will control for any variation in observable characteristics between conditions that remained after the minimization procedure that was used to randomize the students into the conditions. Missing values in the questionnaires will be prevented as the questionnaires are administered through an online secure software program (Enalyzer) in which answering to all items is obligated. The main outcome measure (remaining at school) will be insensitive for missing values as this data can be retrieved from the administration offices of the educational institutes. In case of missing data (for example, when a student does not fill in the second or third questionnaire), intention-to-treat analyses will be performed to account for incomplete outcome data [55]. In addition, it will be examined whether the rates of incomplete data differ between the control and experimental condition. To detect any outliers, the median absolute deviation method will be used [56]. Unrealistic outliers (due to e.g. data entry mistake) will be removed. In case of outliers with a realistic value, we will perform the analyses both with and without the outliers and we will report both results.

Descriptive statistics (e.g. frequencies, means and standard deviations) will be provided for all variables. Conventional statistical tests (e.g. regression, chi-square and ANOVA) will be used to address the research questions in accordance with how the data align with the assumptions of these tests (e.g. normality, homogeneity). In case the data are not normally distributed, the non-parametric equivalents will be used (e.g. the Friedman-test, the Mann-Whitney-test and the Wilcoxon signed-rank test).

With respect to the primary outcome, remaining at school, we will compare the number of students who remained in education or graduated in the experimental and the control condition at T2. Logistic regression models will be conducted to test the differences between the experimental and control condition. In addition, the differences in scores on the secondary outcomes, study success and student satisfaction, will be examined for T0 to T2 using chi squares or repeated measures of variance with the ANOVA test using 95% confidence levels, respectively. Furthermore, the differences between the two conditions on number and duration of contacts with the SEd specialist, the trained staff member or students service provider; the number of study skills where the students need support with and the number of resources needed or used when studying, student general self-efficacy levels and the working alliance with the professional, will be calculated using the ANOVA test with 95% confidence levels. Moreover, to test whether outcomes are similar for students from both educational institutions, sensitivity analyses will be performed excluding students from the institute for intermediate vocational education.

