### Study procedures

We adhere to the SPIRIT 2013 guidelines [40], the checklist is provided in the Additional file 2.

Students who heard about the study through one of the recruitment strategies and are interested in participation, contact the research team by e-mail. A data coordinator will check the inclusion criteria and will then send a link to an online questionnaire which starts with information about the study and the question to fill out an informed consent form. In the informed consent (see Additional file 3), students state that they have been informed about the study and that they participate voluntarily. In addition, they give permission to collect grades and course credits from the school’s administration for the next five years, so we are able to follow the study success of the students after the current project has finished. They also give permission that in case they drop-out of the study, school progress keeps being monitored. Students have the right to withdraw this permission at any moment in time.

After signing the informed consent, the students fill out the baseline-questionnaire. Then, students will receive a student ID number and will be randomized, for both educational institutes separately, by the data coordinator in either the experimental condition (Supported Education-coaching; half of the group of students) or the control condition (support as usual plus advice on potential resources; half of the group of students), using the minimization approach [41] which aims to minimize imbalance between the conditions on specific factors, in our case on gender, age, ethnicity, study year, level of study, the number of credits completed, and level of psychological distress. The condition to which the student is allocated depends on the characteristics of the students that were already enrolled. Students will receive compensation (a gift coupon of 12,50 euro each) for filling in the questionnaires at baseline, 6- and 12-month follow-up. Within this 12-month follow up, each student experiences a critical moment in the educational pipeline: either transitioning to the next year or graduating. In Table 1, the Spirit flow diagram of the study procedure is presented.

**Table 1 Tab1:** SPIRIT flow diagram of the study procedure showing enrolment, interventions, and assessments

	Pre-intervention	Post-intervention (within one month)	6 month follow-up	12 month follow-up
**TIMEPOINT**	**t**_**0**_		***t***_***1***_	***t***_***2***_

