A bottleneck of many RCTs is the low influx of participants [62–64]. Therefore, in this study we will be attentive on the inclusion speed: can a sufficient influx of students be expected per site; is there still a willingness to participate at the various levels of the organization, and are disturbing factors for the project expected (e.g. a reorganization)? In addition, we will closely monitor the influx of students during the recruitment phase by evaluating monthly if recruitment rates are on track, in order to identify potential problems in time and initiate additional actions to boost inclusion.

In order to recruit a sufficient number of students, we asked the advisory board to advise us about relevant recruitment strategies. The recruitment strategies that were mentioned like posts on the internal website of the schools and on social media, posters, information brochures and personal contact with educational professionals will be used in the study.

To increase the chance that we reach a sufficient number of students for our study, we decided that the inclusion period of students is six months. Consequently, there will be differences at baseline being the point in the school year the student is enrolled in the study. However, we expect these differences to be the same in the experimental and control condition. We will report this information and if necessary, we will take it into account during the data analysis.

In addition, the attrition of participants can be a threat to studies in which follow-up measurements are used [63, 65]. In the informed consent form of our study, students give permission to collect information about their school progress (drop-out, grades, and course credits) from the school’s administration system also in case they drop-out of the study. In this way, complete and objective data regarding our primary outcome (remaining in school) and a part of our secondary outcomes (study success) are guaranteed.

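### The plan lets observed imbalance after minimisation choose the covariates of the primary model, instead of fixing a short set in advance that includes institute and key minimisation factors

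*Protocol article*

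**What the plan says.** All places are in the protocol article.

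- **Study procedures, allocation:** students "will be randomized, for both educational institutes separately, by the data coordinator", with "half of the group of students" going to each condition. Minimisation is used to limit imbalance, "in our case on gender, age, ethnicity, study year, level of study, the number of credits completed, and level of psychological distress".
- **Proposed analyses, general rule:** "we will control for any variation in observable characteristics between conditions that remained after the minimization procedure". No covariates are listed, and no size of difference is given that would count as remaining.
- **Proposed analyses, primary outcome:** "Logistic regression models will be conducted to test the differences between the experimental and control condition". No covariate is named here.
- **Proposed analyses, institute:** it appears once, where "sensitivity analyses will be performed excluding students from the institute for intermediate vocational education".
- **Discussion:** because recruitment lasts six months, students enter at different points in the school year. The authors expect this to be alike in both conditions, and add that "if necessary, we will take it into account during the data analysis".

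**The concern.** A covariate belongs in the model of a randomised trial because it predicts the outcome or was used in allocation, not because the arms happen to differ on it. The stated rule turns this round. Minimisation works to balance its own factors, so a rule triggered by leftover imbalance will tend to pass over those factors and pick up other characteristics that differ by chance.

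Two things follow. First, if allocation has balanced prognostic factors and the model ignores them, the model-based standard error overstates the real variability of the estimate. The test becomes conservative and power is lost. Second, the covariate set is known only after the data have been inspected and a threshold chosen, so more than one primary result is compatible with the protocol. In a logistic model the odds ratio being estimated also changes with the covariates, so the target itself is not fixed.

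**Working it through.** The plan gives no figure on this point, so there is none to reproduce. The check is by simulation.

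**Inputs from the protocol article**
- 140 students (Sample size calculation); 102, the number before inflation for study drop-out, as the lower case.
- Two institutes, seven minimisation factors, 1:1 allocation (Study procedures).
- Standardised effect 0.5 (Sample size calculation). On the log-odds scale: 0.5 × π/√3 = 0.907, so OR = exp(0.907) = 2.48.
- School dropout about 15%. This is a five-year figure from a cited study (Background) and is only an assumption for 12 months.

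**Assumptions, not in the documents**
- Binary factors, and minimisation that follows the preferred arm with probability 0.8.
- Institute, five of the seven factors and three of six other baseline characteristics are prognostic, at log-odds 0.4 (moderate) or 0.8 (strong) each.
- Two-sided 5% Wald test in ordinary logistic regression, 2,500 runs per setting. The Monte Carlo standard error near 5% is √(0.05 × 0.95/2500) = 0.4 points.

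**Step 1: how far the rule leaves the model open.** There are 14 candidate characteristics (institute, seven factors, six others). At 140 students, the mean number selected is 4.7, 1.6 or 0.3 if remaining variation means a standardised difference above 0.1, 0.2 or 0.33. At 102 students it is about 6.1, 2.1 and 0.6. With a true effect, the significance verdict was not the same across the unadjusted and three selected models in 9% to 14% of trials; under the null, in 2% to 4%.

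**Step 2: size and power at 140 students.** Selected means a difference above 0.2; all means institute plus seven factors, fixed in advance.

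| Remaining at school (null) | Log-odds per factor | Null rejection %: unadjusted / selected / all | Power %: unadjusted / selected / all | All minus selected |
|---|---|---|---|---|
| 71.7% | 0.4 | 5.1 / 5.5 / 6.2 | 53.7 / 53.0 / 56.5 | 3.5 |
| 68.7% | 0.8 | 4.4 / 4.4 / 6.5 | 44.6 / 44.4 / 52.6 | 8.2 |
| 85.5% | 0.4 | 3.6 / 3.7 / 4.8 | 29.4 / 29.0 / 32.4 | 3.4 |
| 81.9% | 0.8 | 3.2 / 3.4 / 5.3 | 29.8 / 30.4 / 35.9 | 5.5 |

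The selected model behaves almost like the unadjusted one, so the rule recovers little of the benefit of adjustment. Part of the gain of the full model in the first two rows is test size, since it rejects 6.2% and 6.5% under the null.

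**Step 3: a short fixed set.** In a separate simulation (140 students, 2,000 runs, OR 2.48, penalised fit with institute and three factors), power for selection against the fixed set was 39–41% against 39–41% with moderate factors, and 34–35% against 37–38% with strong ones. The gain is about 0 to 3 points, or at most 38 − 34 = 4 across the ends of the ranges.

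**Step 4: analyst freedom under the null.** Taking the smallest p-value of the unadjusted and three selected models at 140 students gave 4.9% to 6.9% rejection, against 3.2% to 5.1% unadjusted.

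**Step 5: room for covariates.** 0.15 × 140 = 21 dropouts from school (0.15 × 102 ≈ 15). Condition, institute and seven factors need at least 9 coefficients: 21/9 = 2.3 events each. The full model failed to converge in up to 2.3% of runs at 140 students and up to 8.6% at 102.

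**The case against.** The strongest objection is that a journal article commonly leaves the covariate list to an analysis plan, so the lack of one is no fault. That stands. For the same reason, a reader might infer that institute and the minimisation factors are excluded from the primary model. The documents do not support this: the primary analysis is silent on covariates, and variation remaining after minimisation can include residual imbalance on the minimisation factors themselves. With seven factors run within two institutes, some of it natural to continuous measures such as age and credits, residual imbalance is plausible. The factors enter conditionally. What survives is that the article does state a selection rule, and an analysis plan that followed it would carry it forward.

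A reader might also infer a power loss of about 8 points, since one simulation gave 29.7% unadjusted against 37.9% with institute and two factors. But an unadjusted analysis is not what is planned, and in the strong-factor null setting of that simulation the adjusted model rejected 6.2% against 3.5%, so part of the gap may be test size.

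Finally, a reader might infer an inflated false-positive rate. The selected models rejected 3.2% to 5.7% under the null at 140 students. Only deliberate picking of the smallest p-value reached 6.9%.

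The sensitivity analysis that drops one institute does not answer the point: it removes students and does not adjust for the stratum.

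**Conclusion.** The point holds in a limited form. The stated rule makes the primary model depend on the data, and it tends to leave out institute and the factors used in allocation precisely when allocation has worked. The expected cost is a mildly conservative test when they are omitted, about 0 to 4 points of power at 140 students against a short fixed set, and a choice left to the analyst.

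The larger differences of 5.5 and 8.2 points arise only when every prognostic factor is assumed strong and all seven factors are fitted, a model that few events may not support. All these sizes rest on assumed prognostic strengths, an assumed form of minimisation and an assumed dropout rate. The defect in the wording does not depend on them.

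**What to change.** In Proposed analyses, replace the imbalance rule with a statement to this effect: the primary logistic model contains condition, institute and a short list of minimisation factors judged most prognostic, named before outcome data are seen and kept whatever the observed balance; no balance checks are used to select covariates. Decide in the same place whether the point in the school year is in the model, in place of the conditional wording in the Discussion.

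Keep the list short, because about 21 events are expected under the 15% assumption. Report the unadjusted model and the model with all minimisation factors as sensitivity analyses, and say how non-convergence of the latter will be handled. Which factors to name, and whether to use a penalised fit, are for the sponsor's statistician.

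The cost is small. Institute and the minimisation factors must be known before allocation, so no students, visits or measurements are added. The downside is a slightly more complex primary model.

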### Sample size calculation

As mentioned before, this is the first RCT on the effect of our SEd intervention on remaining at school, our main outcome measure. Therefore, the effect size of our intervention on remaining at school is unknown. In such cases, it is a common convention to set the effect size at 0.5 [35], because a lower effect size would not be considered as clinically relevant [36, 37]. Therefore, we aim to demonstrate an effect size of 0.5 on the primary outcome measure remaining at school with a power of 80% and an alpha < 0.05.

Hence, for each condition 51 students are needed (total 102). Given an expected drop-out percentage of 25% from the study, 140 students (2 × 70) need to be included in the study. This is a feasible number, considering that 20–45% of students worldwide experience mental health problems [1, 38, 39].

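### Intention-to-treat is offered as the remedy for missed questionnaires, but the repeated-measures ANOVA named for student satisfaction drops students who lack a required wave

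*Protocol article*

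**What the plan says.** All of the following is in the protocol article.

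- **Missing questionnaires (Proposed analyses).** The text names the situation, "when a student does not fill in the second or third questionnaire", and gives the remedy: "intention-to-treat analyses will be performed to account for incomplete outcome data". A literature reference is attached, but no imputation or modelling method is named there or elsewhere in the article.
- **Missing items (Proposed analyses).** The questionnaires run in software "in which answering to all items is obligated", so whole missed questionnaires are the kind of missingness that remains.
- **Check on missingness (Proposed analyses).** In addition, "it will be examined whether the rates of incomplete data differ between the control and experimental condition".
- **Test for satisfaction (Proposed analyses).** The secondary outcomes, study success and student satisfaction, are examined from T0 to T2 "using chi squares or repeated measures of variance with the ANOVA test using 95% confidence levels, respectively". The last word assigns repeated-measures ANOVA to satisfaction.
- **Fallback tests (Proposed analyses).** If data are not normally distributed, the examples given are "the Friedman-test, the Mann-Whitney-test and the Wilcoxon signed-rank test".
- **Expected loss (Sample size calculation).** "Given an expected drop-out percentage of 25% from the study", 140 students (70 per condition) are to be included.
- **Data sources (Abstract, Discussion).** Remaining at school and study success come from school records, also for students who leave the study. Satisfaction comes only from the online questionnaires at baseline, 6 and 12 months.

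**The concern.** The article does not merely leave the missing-data method to a later document. It names a remedy, and that remedy cannot do what is claimed for it. Intention-to-treat is a rule about the analysis set and the arm in which each student is counted. Once a T2 score is absent, some further step is needed to keep that student in the analysis, and the named test has none.

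At stake is hypothesis 3, that students receiving Supported Education are more satisfied at school. Satisfaction is a named secondary outcome and the only one that school records do not protect. The article's own Background links satisfaction to leaving school, so non-response related to satisfaction is plausible. A reader of the results would be told that the comparison is by intention-to-treat when it covers only students who answered.

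**Working it through.** **1. The plan's own recruitment figure.** Inputs from Sample size calculation: 102 students needed, 25% drop-out. 102 / (1 − 0.25) = 136. The article states 140, so its figure is reproduced with slight rounding up.

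**2. Who the named test keeps.** Conventional repeated-measures ANOVA needs a full set of scores per student. The wording T0 to T2 can be read in two ways:

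| Student's pattern | Three waves (T0, T1, T2) | Two waves (T0, T2) |
|---|---|---|
| All three present | kept | kept |
| T1 missing only | dropped | kept |
| T2 missing | dropped | dropped |

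Students missing T2 are lost on either reading. The fallbacks do not solve this. The Friedman and Wilcoxon signed-rank tests also need complete sets, and a Mann-Whitney test at T2 needs the T2 score.

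**3. How many remain.** Number kept = N × (1 − loss), with N = 140:

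- 25% loss (the plan's figure): 140 × 0.75 = 105 kept, 35 randomised students out.
- Range, as an assumption: 10% loss gives 126; 40% loss gives 84.
- If T1 and T2 were each missed independently by 25% (assumption) and three waves are used: 140 × 0.75 × 0.75 = 78.75, about 79.

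**4. What that does to precision.** The article sets its effect size of 0.5 for the primary outcome only. Borrowing it for satisfaction as an assumption, a two-sided two-sample t-test at 0.05 has this power:

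| Students analysed | Power |
|---|---|
| 140 | 0.84 |
| 105 | 0.72 |
| 84 | 0.62 |

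These figures show the scale of the loss. A better method recovers only part of it, because a missed score carries no information of its own.

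**5. Whether bias can be sized.** Suppose T2 loss in the control arm depends on low T1 satisfaction and loss in the other arm is random. If control completers have a mean T1 score δ above the mean of their whole arm, their mean T0-to-T2 change is shifted by (ρ₁₂ − ρ₀₁) × δ, where ρ₁₂ is the T1–T2 correlation and ρ₀₁ the T0–T1 correlation. The result depends on inputs the document does not give:

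- ρ₀₁ = 0.5, ρ₁₂ = 0.75: factor 0.25. In simulation with 32% loss in control and 18% in the other arm, the bias against Supported Education is about 0.06 SD, rising to about 0.09 to 0.10 SD with stronger dependence.
- ρ₀₁ = 0.6, ρ₁₂ = 0.6: factor 0, and simulation shows practically no bias.

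Neither the correlations nor the loss pattern can be checked against the article.

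**The case against.** The strongest reply is that this is a condensed article. The technique for missing data is usually left to the analysis plan, and the sentence cites a source that may describe an imputation step. No sentence says that incomplete students are excluded; the stated intention is the opposite. That limits what can be said about what the investigators will finally do. It does not rescue the text, which pairs a principle that fills no gap with a test that requires complete data.

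The reply also notes that the plan compares missingness rates between arms. It does, but this is a diagnostic: it shows whether loss is unequal and changes nothing in the estimate.

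Three stronger readings are tempting, and the documents do not support them:

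- **That every student missing any questionnaire is dropped.** This holds only if three waves are used. On the two-wave reading, a student with T0 and T2 stays in.
- **That the satisfaction result will be biased against Supported Education, or that loss will differ by arm.** The control condition is active, with regular provider meetings at one site and three meetings plus two phone consults at the other. Both arms receive the same questionnaires and the same coupon. Nothing supports a particular split in loss, and the fifth step of the working shows that the bias can vanish under other assumptions.
- **That a mixed model would be unbiased.** In the first scenario above this is so only if T1 is observed for those who miss T2. If half of them also miss T1, the likelihood-based estimate is off by about 0.06 SD; if all do, by about 0.14 SD, which is more than the completer analysis.

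Reach is also limited. Only satisfaction and the other questionnaire scores analysed over time are touched.

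**Conclusion.** The point holds for the questionnaire outcomes. As written, the analysis of satisfaction would be a completer analysis carrying an intention-to-treat label. At the plan's 25% drop-out it would use about 105 of 140 students. This takes the 25% as loss of a required questionnaire and the ANOVA in its conventional complete-data form.

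The inconsistency and the loss of students follow from the text. The size and direction of bias do not, and no figure for bias should be attributed to this trial. The primary outcome and study success are unaffected. The change should be made before analysis, but it does not threaten the trial's main conclusion.

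**What to change.** Delete the statement that intention-to-treat accounts for incomplete outcome data, keeping intention-to-treat as the definition of the analysis set and arm. Replace the repeated-measures ANOVA with wording along these lines:

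> Satisfaction and the other questionnaire scores measured at T0, T1 and T2 are analysed in all randomised students, in the arm to which they were allocated, using a likelihood-based linear mixed model. T0, T1 and T2 are responses, with baseline means constrained to be equal between conditions. The model includes condition by time, institute, and the covariates for which adjustment is already planned. The contrast between conditions at T2 is the result. A sensitivity analysis shifts the missing T2 values separately in each condition over a stated range.

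Multiple imputation in all randomised students is an acceptable alternative. Treating T0 as a response matters. A model restricted to students with at least one follow-up would still leave out some of those randomised, whereas here they contribute their baseline score. The sensitivity analysis also covers students with no follow-up at all. The planned comparison of missingness rates should stay as a descriptive check. For scores not taken at baseline, such as the working alliance, T1 and T2 are the responses.

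The cost is a change of wording and slightly more analysis work, with no new data collection. The model relies on data being missing at random given the observed scores, which cannot be verified; the sensitivity analysis shows how far the conclusion depends on it.
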